### Qualitative Analysis

NVivo9 computer software will be used to code the transcripts from the focus groups. Emergent themes from the focus groups will then be explored (n=20 from each arm). Transparent validation of emergent themes and content will be performed using 2 coders. Thematic analysis will be performed as such an approach allows for contextual differences between perceptions, experiences, and belief to be developed and explored.

Incremental cost-effectiveness ratio—the ratio of incremental costs to incremental outcome between the test and control group—will be calculated. Incremental outcomes for the cost-effectiveness analysis include differences in number of children treated in primary care settings without the need for specialist pediatric dental referral, the differences in COHRQoL between and within groups, the differences in number and type of treatment provided, re-treatment, and antibiotics for dental infections over the 12-month period. Incremental outcome for cost-utility analysis refers to difference in health utility scale.

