### Evidence

In WA, dental therapists, through the SDS and working in school-based dental clinics, have been the mainstay of successful publicly provided dental care for 5-17-year-old school children since the early 1970s [22]. A recently completed pilot randomized controlled trial in WA showed that primary care delivered by dental therapists trained in the ART approach, compared to standard care (ie, dentists providing treatment using the drill and local anesthesia), reduced the rate of referral for specialist pediatric dental care of preschool children affected by ECC by 44% [23]. The ART-based approach adopted in the study relied on treating carious teeth by removing affected dentine using hand instruments without the administration of local anesthetic. However, a pragmatic approach to treatment was undertaken in that the use of rotary instruments was permitted where a clinician judged that the child was able to cope with the procedure after a period of acclimatization to dental treatment. This pragmatic approach enabled the undertaking of more invasive procedures, beyond what standard ART approach encompassed, such as pulp therapy of deciduous teeth and, in a few instances, tooth extractions.

The study also included a range of preventive interventions including fluoride varnish application to deciduous molars and noncavitated carious lesions as well as oral health counseling using the motivational interviewing approach. The study delivered a “holistic” package of care that considered the needs of the child in total, including preventive care and appropriate skill development of the parent/caregiver to promote oral health. Also, in that study, some children who were scheduled for care under GA were able to be successfully treated using the ART-based approach. The study showed that the COHRQoL was improved after primary dental care with acceptable clinical outcomes [24,25] without adverse effects on childhood dental anxiety. In addition, the approach was cost saving. Hence, the ART-based approach may provide a successful primary model of care, encompassing both treatment and prevention, for children in rural and remote locations where access to GA may not be advisable or readily available.

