### Current Situation

The WA state government is introducing an early childhood preventive program for preschool children (0-4-year-olds) in rural and remote Aboriginal communities by applying fluoride varnish to the primary teeth by Aboriginal health workers trained in the fluoride varnish application. The fluoride varnish program is incrementally being rolled out throughout WA, starting in Kimberley (north-west WA) in 2016. The program is a preventive program, and children requiring dental treatment are referred to the local dental practitioners, either private practitioners or practitioners within the Health Department or Aboriginal Medical Services. While fluoride varnish application has been shown to be efficacious in ECC prevention among Aboriginal children [26], children without adequate access to treatment services may continue to experience untreated disease.

Currently, preschool children (ineligible for SDS care) requiring dental treatment need to source care from private dental practitioners (ie, at their own cost) or, if eligible for subsidized care (ie, liable for co-payments) through government general dental clinics, where restorative care is provided by dentists. Dental therapist and oral health therapists provide mainly dental hygiene services. Subsidized dental care is available to those who are in receipt of certain types of Commonwealth Government benefits (eligibility for the benefits are means tested). The WA government general dental clinics, located mainly in regional cities and major towns, provide clinical care mainly to eligible adults, but children ineligible for SDS and in receipt of specific types of government benefits are able to access care. The location of these clinics in major regional centers means extensive travel for children living in more remote locations to access care. Also, treatment is usually provided using standard care approaches involving the administration of a local anesthetic and using rotary instruments to prepare the cavity.

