### Economic Evaluations

#### Cost-Effectiveness Analysis

Cost-effectiveness of the intervention will be estimated using standard approaches [36] and will be from a health care provider perspective. Effectiveness measures will be the number of children managed in primary care without need for specialist referral, changes in COHRQoL, the numbers and types of treatments provided, and dental caries increments. The economic evaluation will compare any incremental costs of the intervention (ie, costs accrued in the intervention arm compared to those in the control arm) to the full list of incremental primary and secondary outcome endpoints, all expressed in their natural units of measurement. Costs will be measured from activity data with pathway analysis to fully specify all activities in both intervention and control arms. The resource use and dental services utilization will be obtained from research team records and intervention provider records. Measured resource use will be valued using both existing estimates of the costs of each unit of the resource use from market prices and the Dental Benefit Schedule fee rates for nonspecialist and specialist attendances. Standard discounting will be applied to both cost and outcomes. Uncertainty in the cost and outcome data will be subjected to sensitivity analyses.

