### Treatment Procedures

Test children will be provided with care by dental therapists previously trained in and using the ART approach. Treatment will be undertaken at SDS clinics or field settings, using portable equipment. Restorative treatments will be provided using hand instruments principally, without the use of local anesthesia with the cavity prepared and subsequently restored with a glass-ionomer cement. Where extractions are required, the procedure will be undertaken using standard care approaches. All children will also be provided with preventive fluoride varnish applications at treatment and reviewed at 6-month follow-ups. All treatment will be recorded in patient clinic records. At the 6-month reviews, participants will be provided with preventive fluoride varnish and any other necessary care. Children unable to be provided with care will be referred for specialist care. There will be no direct costs incurred by the participants for the primary care.

Control children will be provided with standard care as part of the fluoride varnish program. Children found to require dental treatment will be referred for care through the prevailing care pathway, that is, government dental services or local private practitioners.

In order to ensure all participants are offered the opportunity to access dental treatment, and in keeping with the delayed treatment intervention design, control participants will be offered treatment using the test treatment approach after the 12-month follow-up.

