### Data Analysis

Data will be analyzed on an intention-to-treat (ie, participants analyzed on the basis of their group allocation regardless of whether they received the intended treatment), and per protocol basis (participants analyzed on the basis of their group allocation and receiving the intended treatment). Descriptive statistics will be presented and baseline variables will be compared between groups to test for fairness with respect to the randomization. Aim one (primary outcome) will be tested using test of proportions and logistic regression to control for potentially confounding factors. Changes in health utility and COHRQoL (secondary outcomes) will be tested using paired (within group) and unpaired (between groups) and parametric and nonparametric tests as appropriate, and multivariate analysis using linear regression for continuous variables and Poisson regression for count variables to control for possible intergroup imbalances. Responsiveness of the COHRQoL scale will be determined by calculation of effect sizes for the scale overall and specific domains. Statistical significance will be set at alpha=.05. All analyses will take into account the cluster design and will incorporate multilevel analyses where indicated. Multiple imputation of missing data will be further undertaken to evaluate its impact on the primary and secondary outcomes.

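### Within-group change in quality of life is listed as an incremental outcome for the cost-effectiveness ratio, although the article defines that ratio as test versus control

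*Protocol article*

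**What the plan says.** The ratio is specified in the second paragraph of the Qualitative Analysis section of the protocol article. It is defined there as "the ratio of incremental costs to incremental outcome between the test and control group". The next sentence lists the outcomes that may serve as the increment, and one entry is "the differences in COHRQoL between and within groups".

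The Cost-Effectiveness Analysis section fixes the numerator in the same arm-against-arm way: incremental costs are "costs accrued in the intervention arm compared to those in the control arm". On the outcome side that section is general and does not mention a within-group contrast: "Effectiveness measures will be the number of children managed in primary care without need for specialist referral, changes in COHRQoL", followed by treatments provided and caries increment.

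The Data Analysis section shows how the article uses the two terms. Changes in health utility and quality of life are to be "tested using paired (within group) and unpaired (between groups) and parametric and nonparametric tests as appropriate". Within-group there means a paired before-after comparison in one arm, as distinct from the comparison of arms.

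**The concern.** A change within the test arm is not an increment over control. It mixes the effect of the intervention with whatever would have happened under standard care: ageing of the children, regression to the mean, and shifts in how parents answer. The article recognises the last of these, since its Measures section plans a then-test for response shift in both arms. Randomisation removes such influences only through the comparison with control.

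Aim 3 asks whether the intervention costs less for a similar or greater gain, or costs an affordable amount more per unit gained. Either answer needs the gain over control. A quality-of-life ratio built on a one-arm change would answer a different question, and a reader could mistake it for the incremental result.

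**Working it through.** **The two definitions side by side.** The numerator is test-arm cost minus control-arm cost (Cost-Effectiveness Analysis). The general definition of the denominator is the outcome difference between test and control (Qualitative Analysis). The listed quality-of-life denominator is the difference between groups and also within groups (same paragraph). The within-group part fits neither general definition.

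**Figures in the article.** There is no ratio to reproduce. The article states no incremental cost and no expected quality-of-life change in either arm. The Sample Size section mentions a detectable 33% difference in mean ECOHIS (the quality-of-life scale), but gives no means and no control-arm change. The numbers below are therefore assumptions that show the mechanism.

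**Algebra.** Let I be the incremental cost, and let dT and dC be the improvements in the test and control arms, counted as positive when quality of life gets better.

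- Incremental ratio: I / (dT − dC)
- Within-group ratio (test arm): I / dT
- Within-group divided by incremental: (dT − dC) / dT

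**Illustration** with dT = 4 points, for I = 500 and for I = −200 (all assumed):

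| dC | (dT − dC)/dT | Within, I = 500 | Incremental, I = 500 | Within, I = −200 | Incremental, I = −200 |
|---|---|---|---|---|---|
| 2 | 0.50 | 125 | 500/2 = 250 | −50 | −100 |
| 1 | 0.75 | 125 | 500/3 = 167 | −50 | −67 |
| 0 | 1.00 | 125 | 500/4 = 125 | −50 | −50 |
| −1 | 1.25 | 125 | 500/5 = 100 | −50 | −40 |
| −2 | 1.50 | 125 | 500/6 = 83 | −50 | −33 |

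The within-group ratio is the same in every row because it ignores the control arm. With a positive incremental cost it is 50% too low in the first row, 25% too low in the second, correct in the third, and 25% and 50% too high in the last two. With a negative incremental cost the two ratios still differ, but the size of a negative ratio has no simple reading as better or worse.

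**Control improves more than test.** With dT = 4 and dC = 6 (assumed), the within-group figure shows a gain of 4 points, while the true increment is 4 − 6 = −2. If the intervention also cost less, the within-group version would read as cheaper with a health gain, when the trial had shown a saving bought with a loss. Here the conclusion changes, not only the size of the ratio.

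**The case against.** The best defence is that both general definitions are right, that no sentence says a ratio with a within-group denominator will be calculated or reported, and that the phrase may simply echo the paired and unpaired tests in Data Analysis. It might also mean within-child change compared between arms, which is a proper increment. That last reading is possible but weak: a difference in change between arms is already a between-group difference, so the extra words would add nothing, and Data Analysis uses within-group for the one-arm paired contrast. Even if the authors intend it, the text needs the same edit. It does stand that the between-group ratio is planned as well, and that the article does not make the within-group version its only or main result.

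A reader might infer that the wording makes the intervention look too cost-effective. The documents do not support that as a general statement, because it needs both an improving control arm and a positive incremental cost. Control improvement is plausible: "Control children will be provided with standard care as part of the fluoride varnish program", with referral for those who need treatment. But the Current Situation section warns that "children without adequate access to treatment services may continue to experience untreated disease", so the control arm could also stay flat or worsen. On cost, the Evidence section says of the pilot: "In addition, the approach was cost saving". The direction of the distortion is therefore open.

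A reader might also infer that Aim 3 as a whole depends on this ratio. It does not. Quality of life is one of several effectiveness measures, alongside avoidance of specialist referral, treatments provided, caries increment, re-treatment and antibiotic use. The cost-utility analysis has its own incremental outcome.

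**Conclusion.** The point holds as an internal contradiction: the list of incremental outcomes admits a one-arm before-after change that the article's own definitions of the ratio and of incremental cost exclude. A ratio calculated that way would be off by the factor (dT − dC)/dT. For a positive incremental cost and an improving test arm, that means too low if control improves by less than the test arm, correct if control does not change, and too high if control worsens. If control improves more than the test arm, the sign of the health gain is wrong. The algebra rests on no trial data; the sizes shown rest on assumed costs and changes. Neither a direction nor an expected size can be drawn from the documents. The consequence is confined to the quality-of-life ratio, so this is a correction worth making before analysis and not a threat to the economic evaluation as a whole.

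**What to change.** In the Qualitative Analysis paragraph on the ratio, delete the words that add within-group differences to the list of incremental outcomes. State that the quality-of-life denominator is the test-minus-control difference in change from baseline, estimated with allowance for clustering. Data Analysis already commits all analyses to take the cluster design into account, so this adds no new principle. Report within-group changes descriptively, outside any ratio; the paired comparisons planned in Data Analysis can stay for that purpose. The cost is an edit of the text and one sentence of definition. Data collection, sample size and visits are unaffected.

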### Data Quality Control

Hard copy data will be entered electronically into a database software, and data will be checked at entry. The database will have data validation parameters incorporated to alert for any values that are outside of permissible values. Participants will be contacted to clarify and amend ambiguous or confusing responses. Data cleaning will be undertaken with 2 people, one to scan the data entry and the other to verify from the hard copy.

## Results

Community consultations have been undertaken, and 26 communities have agreed to participate. Fieldwork is in progress to recruit study participants.

## Discussion

### Principal Considerations

Closing the gap in Aboriginal child health is a national priority. A lack of access to dental services by rural and remote Aboriginal communities has been highlighted. The outcomes of the proposed study will address multiple goals of the NHMRC 2013-15 strategic plan, primarily to “improve the health of Aboriginal peoples and Torres Strait Islanders through the support of health research and its translation”. The research team, comprising established oral health researchers and child health researchers working in Aboriginal health, community development, health economists, dental practitioners, and oral health policy makers, will ensure that the findings of the study can be readily translated into policy and practice. Second, the research is driven by provision of care at the primary care level and will test the capacity of the intervention to reduce the need for tertiary care at hospital for a condition that is essentially a preventable hospital admission and to reduce health inequalities. Third, our research proposal supports the NHMRC goal of “healthy start for healthy life” by engaging with Aboriginal families in the provision of dental care by offering treatment and preventive services.

The outcomes will have a direct impact on the COHRQoL for the study participants because all participants in the treatment arms will be provided with an opportunity to receive dental treatment. The research will also have flow-on effects through the demonstration of a model of care with potential applications in other settings throughout Australia, such as aged care facilities and nursing homes and among population with disabilities/special needs. The study also addresses the oral health needs of priority populations identified in the Australian National Oral Health Plan, 2015-2024, specifically, Aboriginal and Torres Strait Islander people. It will also have impacts for other priority populations identified in the National Oral Health Plan, namely, people who are socially disadvantaged or on low incomes, and people living in regional and remote areas.

We will further undertake oral health promotion and community development to ensure sustainability of the oral health promotion activities by engagement with the Aboriginal Communities and community champions. Furthermore, the development of a condition specific health utility scale will be a major advancement in enabling economic evaluation of oral health care programs for young children using a preference-based measure.

We will also employ Aboriginal research assistants who will be trained in dental clinic assisting as well as research processes. They will also participate in the oral health promotion activities and in the process will be trained to undertake community oral health promotion activities, which will add to capability development within Aboriginal communities. We will also disseminate the study findings to the participating communities by holding community forums as well as ad hoc sit-down chats to present study findings and will meet with the Chief Executive Officers of the Aboriginal Communities to report on the study findings as well as provide them with a written report.

### Conclusion

The significance of this study lies in its holistic approach to testing the model of care. Clinical evaluations as well as oral health‒related quality of life evaluations will be undertaken. Cost-effectiveness and cost-utility evaluations will assist in the development of policy options for oral health services for rural and remote communities. The elicitation of caregiver perspectives through focus group interviews will supplement the clinical, psychosocial, and cost-utility evaluations and provide a richer evaluation of the intervention.

## Abbreviations

ART: atraumatic restorative treatment
CHU_9D: Child Health Utility 9D Index
COHRQoL: child oral health–related quality of life
ECC: early childhood caries
ECOHIS: Early Childhood Oral Health Impact Scale
EQ-5D-Y: Euroqol 5D Youth
GA: general anesthesia
HREC: human research ethics committee
NHMRC: National Health and Medical Research Council
QALYs: quality-adjusted life years
SDS: School Dental Service
WA: Western Australia
